### Practice inclusion criteria

Practice inclusion criteria include general medical practices in NHS Fife and NHS Tayside using the INPS Vision clinical IT system (n = 78) and agreeing to participate, and practices that agree to have relevant medication related data to be automatically extracted from their electronic clinical information systems

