### Practice level analysis

The first assumes a practice level analysis, which is the most conservative. Estimated standard deviations are taken from the measured SD in the PINCER trial, and baseline was estimated from a general practice clinical dataset. The number of practices required is estimated to detect a 20% reduction from baseline with power of 80% with a two-sided alpha of 0.05 (Table 1).

**Table 1 T1:** Sample size estimation for practice level analysis

Standard Deviation	Difference 10% to 8%	Effect size	Number of practices
4.0%	2.0%	0.500	34
6.0%	2.0%	0.333	73
7.0%	2.0%	0.286	96

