### Patient level analysis

The second estimate assumes that patient level before and after data is available, and 15 practices are estimated to be needed. The third assumes a patient level analysis with time series data available, with three 'before' and three 'after' data points. Power is clearly adequate with approximately 10 practices (Table 2).

**Table 2 T2:** Sample size estimation for patient level analysis with time series data

Number of practices	Effect size	Power
10	0.25	83%
10	0.50	97%
10	0.75	99%
10	> 1.0	> 99%

From this analysis, it is clear that lack of power is not likely to be an issue. Because we know that there are significant differences between the two health boards in the primary care pharmacy resource available to practices, we expect to see differences in the effect size between Boards. Additionally, the literature indicates that interventions of the kind planned often (but not always) have varying effects in larger versus smaller practices. This therefore allows us to plan for well powered within strata analyses, and we plan to stratify randomisation into four strata (the combination of the two binary variables Tayside versus Fife and larger versus smaller) with 10 in each strata.

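### The unqualified statement that power is adequate is not supported by Table 1 for the secondary practice-level analysis at SDs of 6% or 7%, nor at practice level for strata of 10 practices

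*Protocol article*

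**What the plan says.** The *Sample size* section of the protocol article announces three estimates, all based on a 20% relative reduction.

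- **Practice level (Table 1).** The text introduces it thus: "The first assumes a practice level analysis, which is the most conservative". The target is to "detect a 20% reduction from baseline with power of 80% with a two-sided alpha of 0.05", taken as a fall from 10% to 8%. On the SDs it says: "Estimated standard deviations are taken from the measured SD in the PINCER trial". The first two rows read "4.0% 2.0% 0.500 34" and "6.0% 2.0% 0.333 73"; the third has SD 7.0%, effect size 0.286 and 96 practices.
- **Patient level, before and after.** 15 practices are needed. No inputs are printed.
- **Patient level, time series (Table 2).** About 10 practices are needed, with 83% power at an effect size of 0.25.

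The conclusion is "From this analysis, it is clear that lack of power is not likely to be an issue". The same paragraph goes on to plan adequately powered analyses within four strata (health board by list size) of 10 practices each.

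*Randomisation and allocation concealment* assumes 40 practices. *Statistical methods* makes the patient-level analysis primary and the practice-level analysis secondary. The practice-level analysis has its own null hypothesis and a test of intervention by health board, and is repeated for all secondary measures.

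**The concern.** The power statement names no analysis and no SD, so it covers the practice-level analysis too. Yet 40 practices satisfy only the first of the three rows of Table 1. The strata claim goes further, because a stratum holds a quarter of the practices.

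Table 1 is also the only one of the three estimates that can be checked from the article. Its result depends on what the listed SD measures, and the article does not say. A reader who relies on the statement could take a null practice-level result, or a null result within one stratum, as evidence of no effect when the analysis had little chance of finding the planned one.

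**Working it through.** **Inputs.** From the practice-level sample-size section: difference 2.0 percentage points (10% to 8%), SD 4%, 6% or 7%, two-sided alpha 0.05, power 80%. From the randomisation section and the strata plan: 40 practices in all, 10 per stratum.

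**Step 1: reproduce Table 1.** Effect size d = 2/SD = 0.500, 0.333, 0.286.

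- Normal approximation for a paired (one-sample) test: n = (1.960 + 0.842)²/d² = 7.849/d². This gives 31.4, 70.6 and 96.15, so 32, 71 and 97. With the printed 0.286 the third is 95.96, so 96.
- Exact paired t-test (noncentral t, n − 1 degrees of freedom, noncentrality d√n): 34, 73 and 99. With the printed 0.286 the third is 98.
- A two-sample comparison gives 63, 142 and 193 per arm, which does not fit.

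Table 1 is therefore a paired before-after calculation. Rows 1 and 2 match the exact t-test, while row 3 matches the normal approximation. The listed SD plays the part of the SD of within-practice change.

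**Step 2: power with the planned numbers**, same paired t-test, listed SD taken as the SD of change:

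| SD of change | N in Table 1 | d√40 | Power, 40 practices | d√10 | Power, 10 practices |
|---|---|---|---|---|---|
| 4% | 34 | 3.16 | 87% | 1.58 | 29% |
| 6% | 73 | 2.11 | 54% | 1.05 | 16% |
| 7% | 96 | 1.81 | 42% | 0.90 | 13% |

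Forty practices reach 80% power only if the SD of change is at most about 4.4%.

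**Step 3: if the listed SD is instead a between-practice SD (assumption).** Then SD of change = SD × √(2(1 − ρ)), where ρ is the before-after correlation, which the article does not give. At ρ = 0.5 the multiplier is 1, so Table 1 as printed amounts to assuming ρ = 0.5.

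| ρ | Multiplier | N needed (SD 4/6/7%) | Power, 40 practices | Power, 10 practices |
|---|---|---|---|---|
| 0.3 | 1.183 | 46/101/137 | 74%/41%/32% | 22%/13%/11% |
| 0.5 | 1.000 | 34/73/99 | 87%/54%/42% | 29%/16%/13% |
| 0.8 | 0.632 | 15/31/41 | 99.8%/90%/79.6% | 61%/32%/25% |

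On this reading 40 practices give 80% power once ρ is at least about 0.39, 0.73 and 0.80 for the three SDs. Ten practices fall short of 80% in every row, even at ρ = 0.8.

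**The case against.** The strongest reply is that the sentence closes the whole sample-size section, not Table 1 alone. It follows the patient-level estimates of 15 and about 10 practices. Those belong to the primary analysis and lie well below 40. The strata of 10 appear to take their size from Table 2. A reader might infer that the statement contradicts Table 1; it does not, because the article nowhere says that 40 practices give 80% power at practice level for an SD of 6% or 7%. This part of the reply stands. It does not show adequate power at practice level. The patient-level figures also cannot be checked from the article: no intracluster correlation or cluster size is given, and the effect size in Table 2 is neither defined nor tied to 10% versus 8%. That makes them unverified, not wrong.

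Other stronger readings also fail:

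- **That Table 1 uses the wrong kind of SD.** The text does not say which SD was measured. If it is a between-practice SD, the table is too pessimistic whenever ρ exceeds 0.5, and at 0.8 the shortfall with 40 practices nearly vanishes.
- **That the label in "The first assumes a practice level analysis, which is the most conservative" is false.** Among the three estimates listed, 34 to 96 practices is the most demanding. The label makes no claim about a model with a time term.
- **That 96 practices is impossible because only 78 use the required IT system.** A pessimistic row need not be recruitable.
- **That row 3 is a material error.** The figures 96, 98 and 99 all far exceed 40.

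The reply can add that the planned 20% effect is modest beside the 40% fall in the pilot practices. At a 4-point difference, 40 practices give 94% power even with an SD of change of 7%. That is fair context, but the stated design target is 2 points.

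**Conclusion.** The point holds in limited form. For the secondary practice-level analysis, Table 1 supports adequate power with 40 practices at an SD of 4% (87%) but not at 6% (54%) or 7% (42%). At practice level it does not support the claim for strata of 10 (29%, 16% and 13%).

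These figures assume a paired t-test, a 2-point difference and the listed SD as the SD of change. If the SD is between-practice, the shortfall with 40 practices is larger below a correlation of 0.5 and smaller above it, and has all but gone at 0.8. The shortfall with 10 practices remains at 0.8. The paired test neither credits the repeated eight-weekly measurements of the planned mixed model nor charges for a time term, so the figures check Table 1 on its own terms and do not forecast the power of the final model.

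Nothing here shows that the primary patient-level analysis is underpowered.

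**What to change.** - Limit the statement that power is adequate to the primary patient-level analysis, conditional on its own estimates, and to the practice-level SDs that 40 practices support.
- Add two columns to Table 1 with the power of 40 practices and of 10 per stratum. On the present inputs these are 87%, 54% and 42%, and 29%, 16% and 13%.
- State whether the SD is between practices or of within-practice change. If it is between practices, state the assumed before-after correlation and recompute both columns.
- Withdraw or qualify the within-strata claim at practice level.
- Compute row 3 by the same method as rows 1 and 2: 99, or 98 with the rounded effect size.
- The description of the practice-level estimate as the most conservative may stay, as a comparison with the other two.

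The cost is a revision of text and one table. No extra practices and no design change are needed. The stated practice-level power becomes less favourable on the present inputs.

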### Randomisation and allocation concealment

The practice will be the unit of allocation, with practices randomised to an intervention start date using a stepped wedge design. On the assumption that forty practices are recruited, four practices will be allocated to each start date, and randomisation will be stratified in order to ensure balance across time points in terms of:

1. Health board (NHS Tayside and NHS Fife). The rationale is that the underlying organisational context differs, particularly in the way that primary care pharmacy and prescribing advice is organised, and in the focus of prescribing improvement work.

2. List size (larger versus smaller practices). The rationale is that there is evidence that complex interventions may be more difficult to implement in larger practices [19]

3. The stepped wedge randomisation will be computer-generated by the statistician on the project (PD) blinded to practice identity, subsequent to which the core research team (TD, AG, and BG) and participating practices will be informed of their start date.

### Blinding

Due to the nature of the intervention, it is not possible to blind either practices or the core research team (TD, AG, and BG). However, outcome assessment is entirely objective and automated. It is also not possible to blind the analyst because the analysis is a time series in which every practice receives the intervention rather than a comparison between groups. The main analysis will therefore be pre-specified rather than blinded, and any analysis not pre-specified will be clearly identified as such and therefore hypothesis generating/exploratory rather than hypothesis testing/explanatory.

### Outcome measures

The outcome measures used are shown in detail in Tables 3, 4, 5, 6, 7 and the levels of analyses (practice versus patient level) are outlined under 'statistical methods'.

**Table 3 T3:** Primary outcome measure (CPO = Composite prescribing outcome)

Number Risk factor (Denominator)		High-risk prescription definition (Numerator)
CPO	Number of patients with any risk factor listed in PO-measures 1 to 9 (Table 4)	Number of patients with any high-risk prescription listed in PO-measures 1 to 9 (Table 4)

**Table 4 T4:** Secondary outcome measures (PO = Prescribing outcomes)

Number Risk factor (Denominator)		High-risk prescription definition (Numerator)
PO-1	Number of patients with a Read Code for peptic ulceration ever recorded	Number of denominator patients prescribed a traditional oral NSAID^¶ ^or low dose aspirin in the previous eight weeks who have NOT been prescribed a gastro-protective drug in the 12 weeks before, or since the most recent NSAID or aspirin prescription
PO-2	Number of patients aged 75 and over	Number of denominator patients prescribed a traditional oral NSAID^¶ ^in the previous eight weeks who have NOT been prescribed a gastro-protective drug in the 12 weeks before, or since the most recent NSAID prescription
PO-3	Number of patients aged 65 and over prescribed aspirin in the previous 12 weeks	Number of denominator patients prescribed a traditional oral NSAID^¶ ^in the previous eight weeks who have NOT been prescribed a gastro-protective drug in the 12 weeks before, or since the most recent NSAID or aspirin prescription
PO-4	Number of patients aged 65 and over prescribed aspirin in the previous 12 weeks	Number of denominator patients prescribed clopidogrel in the previous eight weeks who have NOT been prescribed a gastro-protective drug in the 12 weeks before, or since the most recent aspirin or clopidgrel prescription
PO-5	Number of patients prescribed warfarin in the previous 12 weeks	Number of denominator patients prescribed a traditional oral NSAID¶ in the previous eight weeks who have NOT been prescribed a gastro-protective drug in the 12 weeks before, or since the NSAID prescription
PO-6	Number of patients prescribed warfarin in the previous 12 weeks	Number of denominator patients prescribed low dose aspirin or clopidogrel in the previous eight weeks who have NOT been prescribed a gastro-protective drug in the 12 weeks before, or since the aspirin or clopidogrel prescription
PO-7	Number of patients with a QOF heart failure code ever recorded	Number of denominator patients prescribed any oral NSAID in the previous eight weeks
PO-8	Number of patients prescribed both a diuretic and an ACE inhibitor/ARB in the previous 12 weeks	Number of denominator patients prescribed any oral NSAID in the previous eight weeks
PO-9	Number of patients with a QOF CKD (stage 3, 4, or 5) code recorded as the most recent CKD code	Number of denominator patients prescribed any oral NSAID in the previous eight weeks
PO-10	**GI risk composite** Number of patients with any risk factors as defined in PO-measures 1 to 6	Number of denominator patients with any high-risk prescription as defined in PO-measures 1 to 6
PO-11	**Renal risk composite** Number of patients with any risk factors in PO-measures 8 to 9	Number of denominator patients with any high-risk prescription as defined in PO-measures 8 to 9

^¶ ^'Traditional' NSAID means all representatives of this class *except *Cox-2 selective agents, such as celecoxib;

**Key: **NSAID = Non-steroidal anti-inflammatory drug; QOF = Quality and outcomes framework; CKD = chronic kidney disease; ACE = angiotensin converting enzyme; ARB = Angiotensin Receptor Blocker

**Table 5 T5:** Secondary outcome measures (Repeated versus new prescribing)

Number	Risk factor (Denominator)	High-risk prescription definition (Numerator)
CPO- Repeated	Number of patients with any risk factor listed in PO-measures 1 to 9 (Table 4)	Number of patients with any high-risk prescription listed in PO- measures 1 to 9 (Table 4) where the patient has received a high-risk prescription in the previous 12 months
CPO-New	Number of patients with any risk factor listed in PO-measures 1 to 9 (Table 4)	Number of patients with any high-risk prescription listed in PO-measures 1 to 9 (Table 4) where the patient has NOT received a high-risk prescription in the previous 12 months

**Table 6 T6:** Secondary outcome measures (AO = Admissions outcomes)

Number	Denominator	Numerator
		Trigger event plus high-risk prescription

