**Figure 2 F2:**
[figure not shown]
**Illustration of intervention components and desired impact on prescribing behavior**.

Intervention component one: Informatics tool

The informatics tool is central to the intervention, and will involve the extraction of existing GP clinical data to an NHS Tayside database accessible to the DQIP informatics tool developed by Aridhia (an IT company contracted by NHS Tayside for this purpose). The informatics component will:

1. Summarise numbers of patients affected by high-risk prescribing at practice level based on nine validated measures and one composite measure (see outcome measures). This will allow each practice to monitor trends in high-risk prescribing before and after the start of the DQIP intervention.

2. Identify patients affected by high-risk prescribing for review by the practice, and allow practices to select which patients to target first (e.g., patients triggering particular measures, patients triggering multiple measures).

3. Structure clinical information to facilitate review. All decisions about prescribing and organisation of work around DQIP remain a practice responsibility, including deciding which professional is most suited to do any initial record-based review and any follow-up telephone or face-to-face review.

4. Record review decisions using structured data that supports re-identification of patients if necessary, and to measure trial processes for evaluation.

5. Support reminders to practices to review their data via e-mail reminders.

6. Support the educational intervention (provide general information/summaries of the evidence of risk, links to more detailed reference information, prevalence measurement, and run charts for each practice).

The DQIP informatics tool will additionally collect data for trial process evaluation and record data to trigger practice payment at the end of the trial.

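### PO-9 reads CKD from the latest code, which practices can change during tool-prompted review, so any excess downward re-coding would count as reduced high-risk prescribing; the effect on the composite is probably modest

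*Protocol article*

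**What the plan says.** In the protocol article, Outcome measures, Table 4, the PO-9 denominator is "Number of patients with a QOF CKD (stage 3, 4, or 5) code recorded as the most recent CKD code" and its numerator is "Number of denominator patients prescribed any oral NSAID in the previous eight weeks". The numerator is thus a subset of the denominator. The other two measures that rest on a diagnosis use a rule that a later code cannot undo: PO-7 has "Number of patients with a QOF heart failure code ever recorded" and PO-1 has "Number of patients with a Read Code for peptic ulceration ever recorded". PO-9 feeds the renal composite (PO-11) and the primary composite (CPO, Table 3).

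Under Intervention component one, the tool is to "Identify patients affected by high-risk prescribing for review by the practice" and "Structure clinical information to facilitate review". The practice organises the work, "including deciding which professional is most suited to do any initial record-based review". According to Trial design and Table 8, practices have the tool only from their own start date. Under Data collection, outcomes are measured in this same tool, and the before measures are built at the initial extraction.

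Blinding says that practices cannot be blinded and adds: "However, outcome assessment is entirely objective and automated". The patient level analysis under Statistical methods recognises that patients enter and leave the risk group, but handles this only as correlation between repeated measurements.

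**The concern.** A PO-9 numerator patient can leave the measure in two ways: the NSAID stops, or a newer CKD code takes the patient out of stages 3 to 5. Only the first is the effect that the trial wants to measure. The outcome counts both alike.

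The second route need not be equally common in the two periods. After the start, an unblinded practice is shown the patients who have both the CKD code and an NSAID, and is paid for each patient reviewed. Patients with the code, no NSAID and no other trigger are not shown. A reviewer who finds a CKD code out of date may enter a newer one, and such corrections would fall mainly on numerator patients. Automated reading of the record gives no protection here, because the practice writes the record that is read.

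Any excess would begin at each practice's own start date. Because start dates are staggered, terms for eight-week calendar periods would not absorb it, nor would the random effects. It would go into the before-versus-after term, in favour of the intervention.

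**Working it through.** **The plan's own yardstick.** Table 1 plans on a fall from 10% to 8%, a 20% relative reduction. Its sample sizes can be reproduced closely: n = ((1.960 + 0.842)/effect size)² gives 32, 71 and 97 practices for SDs of 4%, 6% and 7%, against 34, 73 and 96 in the table. A paired t version gives 34, 73 and 99. No figure in the plan is disputed; the 10% and the 20% serve only as reference values.

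**Direction.** With a numerator patients among b denominator patients, removing one patient from both gives (a − 1)/(b − 1), which is below a/b whenever a < b. Downward re-coding of numerator patients therefore always lowers the rate.

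**Size for PO-9.** Let p be the rate and x the share of numerator patients re-coded out. The new rate is p(1 − x)/(1 − px), so the relative fall is 1 − (1 − x)/(1 − px).

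Assumed inputs, none of them in the documents: 70% of flagged patients reviewed, 5–15% of those re-coded, and p of 5–10%. Then x = 0.70 × 0.05 = 3.5% to 0.70 × 0.15 = 10.5%.

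| x | p = 5% | p = 10% |
|---|---|---|
| 3.5% | 1 − 0.965/0.99825 = 3.3% | 1 − 0.965/0.9965 = 3.2% |
| 10.5% | 1 − 0.895/0.99475 = 10.0% | 1 − 0.895/0.9895 = 9.6% |

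**Size for the composite.** Re-coding matters here only for patients who count through PO-9 alone.

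- A patient aged 75 or over on a traditional NSAID without gastro-protection still counts through PO-2.
- PO-9-only patients do exist. PO-9 has no gastro-protection exemption, so a CKD patient on a gastro-protected NSAID who meets neither PO-7 nor PO-8 counts through PO-9 alone.
- If that patient is 75 or over, age keeps the patient in the composite denominator after re-coding, and only the numerator falls.

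Let q be the PO-9-only share of composite numerator patients, assumed to be 10–30%. At a 10% composite rate:

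| q | x | q·x | Leaves numerator and denominator | Leaves numerator only |
|---|---|---|---|---|
| 10% | 3.5% | 0.35% | 1 − 0.9965/0.99965 = 0.3% | 0.35% |
| 30% | 10.5% | 3.15% | 1 − 0.9685/0.99685 = 2.8% | 3.15% |

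The composite thus moves by about 0.3–3% in relative terms. As a share of the planned effect this is 0.3/20 = 1.5% to 3/20 = 15%.

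**How much re-coding would mimic the whole planned effect?** Going from 10% to 8% needs (0.10 − 0.08)/(0.10 × 0.92) = 21.7% of composite numerator patients to be re-coded out. With q = 10% that is impossible. With q = 30% it needs 21.7/30 = 72% of the PO-9-only patients.

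**The case against.** The strongest reply is that the mechanism is conjecture. No section says that practices correct CKD codes, are asked to, or can do so through the tool. Payment follows the review whatever is decided, so re-coding earns nothing extra. This stands: the documents establish a possibility, not a frequency.

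Nor do the documents say that codes stay untouched before the start. PO-9 uses a QOF code, and the protocol mentions the QOF reporting year, so routine re-coding in the before period is plausible. Only an excess during the intervention biases the comparison. Record review could also add or raise a CKD code, so the direction is certain only for net downward re-coding.

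A reader might infer that re-coding could supply up to half of the planned 20% reduction. That compares the PO-9 figure, 3–10%, with an effect planned for high-risk prescribing overall; for the composite the share is about 1.5–15%, on assumed inputs. A reader might also extend the point to PO-1 and PO-7. Their ever-recorded rule means that a newer code cannot remove a patient; they would be exposed only if historical codes were deleted, which no section suggests.

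The statement on blinding does not claim that the underlying records are immune to change. Current-status coding is also a defensible choice for measures described as previously validated.

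Finally, such derivation detail often belongs in the analysis plan, which is promised before data lock and is not shown. That is a fair reason to leave the main definition alone. But Table 4 itself fixes the reversible rule, and neither safeguard in the article separates an exit by re-coding from a change in prescribing.

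**Conclusion.** The point holds as a limited weakness in an outcome definition. PO-9 membership can be reversed by the unblinded practice, and the prompt to look at the records of numerator patients exists only after the start. Any excess of downward CKD re-coding during the intervention would be reported as less high-risk prescribing.

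The size cannot be derived from the documents. Under the assumed inputs it is about 3–10% relative for PO-9 and about 0.3–3% for the composite. PO-11 is more exposed than the composite to the extent that more of its numerator patients count through PO-9 alone. This would not by itself produce the planned 20% reduction, but it could colour the reading of PO-9 and PO-11 and of a small composite effect.

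**What to change.** Keep the as-recorded definition for the tool and for the main analysis. Add to the pre-specified analyses, before data lock:

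1. A sensitivity analysis of PO-9, PO-11 and the CPO in which CKD status cannot be reversed in either period. A patient is at risk from the date of the first stage 3–5 code onwards, parallel to the rule already used in PO-1 and PO-7.
2. A count of numerator patients who left by CKD re-coding in the 48 weeks before and the 48 weeks during the intervention.

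The rule should apply to both periods. Blocking exits only after the start would keep a validly down-staged patient in the during period who would have left in the before period, and so would bias against the intervention.

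The cost is a little more derivation work on dated codes. Some patients whose CKD code was truly out of date stay in the risk group, by the same rule in both periods. If a code is deleted instead of superseded, the rule works only if the earlier extract still holds it, so dated codes should be kept as first extracted.

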### Data collection

#### Prescribing outcomes (PO - 1 to 9)

The primary outcome and prescribing secondary outcomes will be measured in each practice at eight weekly intervals (reflecting that the measure numerators are all for high-risk prescriptions in the last eight weeks). At the time of initial data extraction, eight weekly measures will be constructed for the 48 weeks before the intervention start date.

All outcomes will be measured in the informatics tool using identifiable patient data, but only practices will be able to view identifiable data which will remain in an NHS Tayside controlled database. Access to identifiable data will require explicit practice consent for each individual using the tool, and will be controlled by the NHS Tayside LDAP system used for all clinical systems.

During the study, the core research team will be able to view aggregate practice data (run charts of change over time for each measure) and a summary of practice activity (log-ins, reviews, actions taken). At the end of the trial, fully anonymised data will be extracted from the informatics tool database held by NHS Tayside, and transmitted to the research team using established University of Dundee Health Informatics Centre (HIC) Standard Operating Procedures (SOPs) that require robust anonymisation, transmission using appropriate secure encryption, storage of data on securely encrypted computers, and compliance with Data Protection Act regulations.

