### Design of outcome measures

The DQIP intervention is designed to change prescribing behaviour in primary care and thus, our primary outcome measure and the majority of secondary outcome measures are designed to reflect such behaviour changes.

The core of the intervention is to review existing high-risk prescribing, but we are also hypothesising a reduction in 'new' prescribing, via the triggering of internal practice processes similar to those that appear to have happened with QOF, where stimulating internal monitoring/surveillance have been important mediators of change [21-24]. We do not have any direct control over these internal processes, but will explore their impact by measuring both change in existing prescribing (patients who have received a targeted high-risk prescription in the previous 12 months) and change in 'new' prescribing (patients receiving a targeted high-risk prescription who have not received one in the previous 12 months).

Although not a primary outcome in this trial, the ultimate aim of changing practitioner behaviour is to improve outcomes for patients. However, prescribing is only one among other healthcare process that (in addition to patients' underlying risk factors) may influence outcomes, which implies that interventions focussing on medication use only are unlikely to significantly alter overall mortality or hospital admission rates. Nevertheless, such outcome measures have been used in a number of trials seeking to assess the impact of medication review interventions [25]. We have therefore designed measures that may more specifically capture the potential impact of the DQIP intervention on patient outcomes, i.e., NSAID and antiplatelet specific hospital admissions that are preceded by high-risk prescribing of these agents (AO 1 to 3). Because state-of-the-art assessment of causality and preventability of adverse drug events over the duration of a trial is usually not feasible (clinical judgement by two or more independent experts is usually required), the outcome measures of the type used here may inform the design of similar trials of interventions seeking to improve and measure changes in drug therapy outcomes.

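### CPO-Repeated is not a clean measure of change in existing prescribing: its all-at-risk denominator and moving 12-month look-back let a fall in new prescribing carry partly into it

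*Protocol article*

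**What the plan says.** Objective 2 (Trial objectives) lists repeat versus new prescribing among the secondary outcomes. In Table 5 (Outcome measures) both measures have the same denominator: "Number of patients with any risk factor listed in PO-measures 1 to 9 (Table 4". The numerators are split by history. CPO-Repeated counts patients with a high-risk prescription "where the patient has received a high-risk prescription in the previous 12 months"; CPO-New counts those "where the patient has NOT received a high-risk prescription in the previous 12 months".

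Under Prescribing outcomes (PO - 1 to 9), the prescribing measures "will be measured in each practice at eight weekly intervals", and for the baseline "eight weekly measures will be constructed for the 48 weeks before the intervention start date". No fixed date is given for the 12-month history, so it moves with each measurement.

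Design of outcome measures gives the purpose. Review of existing prescribing is the core of the intervention, but "we are also hypothesising a reduction in 'new' prescribing" through internal practice processes. It continues: "We do not have any direct control over these internal processes, but will explore their impact by measuring both change in existing prescribing" and change in new prescribing. Existing prescribing is described there by the group of patients with a prescription in the previous 12 months, but Table 5 does not use that group as a denominator.

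**The concern.** A patient counted in CPO-New in one window can only count in CPO-Repeated if prescribed again in the windows that follow. If the intervention prevents starts and does nothing else, fewer patients enter the recently exposed group. CPO-Repeated then falls although existing users are re-prescribed exactly as before.

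The error favours the component that the protocol calls its core: a null effect on existing users would look like a modest benefit that grows over follow-up. A fall in CPO-Repeated taken alone therefore does not show that patient review worked.

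**Working it through.** The protocol states no figure for either measure, so there is none to reproduce.

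**Inputs from the protocol article.** Windows of eight weeks and 48 weeks of intervention, so 48/8 = 6 windows (Prescribing outcomes; Figure 1 legend). Look-back of 12 months, 52/8 = 6.5 windows, run as L = 6 and L = 7. Baseline composite p = 10% (Table 1). Planned relative reduction 20% (Sample size).

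**Assumptions, not in the documents.** A closed at-risk population. The chance of a high-risk prescription in a window is c = 50, 70 or 90% after a window with one (continuation), g = 5 or 10% if the last one was earlier in the look-back (restart), and i if there was none in the look-back (initiation). i is set so that the composite is 10% at steady state.

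**Step 1, the identity.**

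CPO-Repeated = (recently exposed / at risk) × (re-prescribed / recently exposed)

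CPO-New = (not recently exposed / at risk) × i

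A change in i alters the first factor of CPO-Repeated from the next window on.

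**Step 2, one case by hand (c = 0.7, g = 0.05, L = 6).** At steady state:

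- CPO-New = p(1 − c)(1 − g)^(L−1) = 0.10 × 0.3 × 0.95^5 = 2.32%.
- CPO-Repeated = 10 − 2.32 = 7.68%.
- Recently exposed = 10% + 3% × (1 − 0.95^5)/0.05 = 23.57%, so i = 2.32/76.43 = 3.04%.

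Now cut i by 20% and leave c and g alone. In window 1 CPO-Repeated does not change, because all history predates the start. In window 2 there are 0.20 × 2.32 = 0.464 points fewer recent starters, of whom 70% would have been re-prescribed: 0.325 points, and 0.325/7.68 = 4.2%. Carrying the recursion on gives falls of 0, 4.2, 7.2, 9.3, 10.9 and 12.1%, mean 7.3%.

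**Step 3, the whole grid (ranges over c, g and L).**

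| Scenario | CPO-Repeated, window 1 | CPO-Repeated, mean | CPO-Repeated, window 6 | CPO-New, mean |
|---|---|---|---|---|
| Initiation −20% only | 0% | −2.3 to −8.8% | −4.3 to −13.1% | −17.8 to −19.8% |
| Initiation −50% only | 0% | −5.6 to −22.5% | −10.7 to −34.5% | −46.5 to −49.6% |
| Continuation and restart −20% only | −20% | −27.5 to −42.6% | −30.4 to −56.4% | +0.1 to +0.5% |

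In the third row CPO-New is up by 0.1 to 1.4% in window 6.

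**Step 4, a different parameterisation.** Give everyone with a history in the look-back one common re-prescribing rate, and let new patients make up 10 to 50% of the composite. A 20% fall in initiation then lowers CPO-Repeated by 1.5 to 4.9% on average and 3.0 to 9.4% in window 6. A 20% fall in re-prescribing lowers CPO-Repeated by 20.8 to 21.7% on average and raises CPO-New by 0.7 to 1.3% (1.9 to 3.2% in window 6).

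**Step 5, separate denominators.** In the model of step 4 the carry-over vanishes: a 20% fall in initiation gives 0.0% in CPO-Repeated and −20.0% in CPO-New, and a 20% fall in re-prescribing gives the reverse. On the grid of step 3 a residual remains in CPO-Repeated, 0.4 to 3.5% on average for a 20% fall in initiation and about 1 to 10% for a halving. It arises because the exposed group mixes current and lapsed users, and fewer starters changes that mix.

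**The case against.** - **The shared denominator is a legitimate choice.** It splits the primary composite into two population rates that add up, and a lower rate of repeat prescribing because fewer patients started is a real fall. This stands for description. It does not stand once the measure is read as a change in the management of existing users.
- **CPO-New carries the question about internal processes.** The exploratory purpose in Design of outcome measures refers mainly to those processes, and CPO-New tracks initiation closely. That is fair, but the same sentence also offers a measure of change in existing prescribing, and that is the measure affected.
- **The two mechanisms leave different traces.** A reader might infer from Table 5 that they cannot be told apart. The calculations do not support this: an initiation effect gives nothing in the first window and a slow drift after it, while a re-prescribing effect shows at once and hardly moves CPO-New. Both series are measured every eight weeks. Nor does it follow that the trial would credit patient review wrongly; that needs someone to read CPO-Repeated alone.
- **The look-back is longer than follow-up.** A reader might infer that stopped patients cannot return to the new group within 48 weeks, so that the carry-over is strictly one-way. Patients whose last prescription was some months before the start do pass 12 months during follow-up, hence the small rise in CPO-New in steps 3 and 4.
- **A formal analysis plan is promised before data lock.** It may refine the analysis, but the article itself fixes these denominators.

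**Conclusion.** The point holds as partial confounding of a named secondary outcome. CPO-Repeated as defined mixes how many patients were recently exposed with how often they are re-prescribed, so it is not a clean measure of change in existing prescribing.

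For a 20% fall in initiation alone the spurious fall is about 2-9% on average and 4-13% in the last window; for a halving it is about 6-23% and 11-35%. The direction and the growth over follow-up follow from the definition. The sizes rest on assumed continuation and restart rates, and the parameterisation of step 4 gives smaller ones. The halving is a strong scenario and should not be set beside the planned 20% reduction in the composite as if the two were alike. The primary outcome is not touched.

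**What to change.** In Table 5, at each eight-week measurement:

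- **CPO-Repeated:** use as denominator the at-risk patients with a high-risk prescription in the previous 12 months.
- **CPO-New:** use as denominator the at-risk patients without one.
- **Present versions:** keep them, labelled as an additive split of the primary composite.
- **Optional sensitivity analysis:** follow a cohort exposed before a fixed anchor date, with time since anchor in the model. It should not replace the main measure, because it leaves out patients who start during the 48 weeks and brings in a decline with time since anchor.

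The cost is a change of definition and some programming; Statistical methods already provides for patient-level data. The two conditional rates will no longer sum to the composite, and the small residual in step 5 remains where continuation and restart rates differ. The change should be made before data lock, since Blinding says that analyses not specified in advance will be labelled exploratory.
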